**Figure 2 F2:**
[figure not shown]
Data collection time points and variables in both the control and intervention phases. BMI, body mass index; NRS, numeric rating scale; PicPecc, pictorial support in person-centred care for children.

Primary outcome:

The change in the primary outcome variable (distress) from baseline (T0) to 48 hours after treatment start (T2) measured on an 11-point NRS (0 (no distress) and 10 (worst possible distress))^42 43^ will be compared between the control and intervention phases. Self-reported distress (NRS-11) will also be collected 4 hours before high-dose methotrexate (T-1) and after 24 hours (T1) (figure 2) in order to establish within subject variation.

Secondary outcomes:

Blood samples will be collected and steroid levels in plasma will be monitored. Pain and steroid levels in blood: neuropeptides, neurosteroids and peripheral steroids will be collected before start (T-1 and T0) of the high-dose methotrexate treatment, 24 hours after start (T1) and 48 hours after start (T2). Since blood-drawing procedures are part of routine monitoring of cancer care, a small sample of the blood will be obtained for this research, with no additional needle pricks required. Steroids are measured in this study using Liquid chromatography tandem mass spectrometry and Super critical fluid chromatography tandem mass spectrometry (LC-MS/MS and SFC-MS/MS) methods.^44^ It is not possible to distinguish between different types of stress, but the design includes the evaluation of two indicators of stress response, first, biological (measured by biomarkers), and second, perceived (self-reported). Since the same individual is assessed before and after the chemotherapy, both with and without the PicPecc tool, it is possible to evaluate the effect of the PicPecc tool on intervention-related stress.Self-reported person centredness. This is evaluated on the VCM,^45^ which will be collected 48 hours after the start (T2) of the high-dose methotrexate treatment. The VCM provides the legal guardians of children <7 years old (VCM 10Q-legal guardians), children aged 7–11 years (VCM 5Q) and adolescents aged 12 years and over (VCM 10Q) the opportunity to report their experiences regarding both the meeting with the healthcare professional and their participation in decision related to healthcare.^45^Frequency of assessments of symptoms with the PicPecc tool. In-app assessment levels will be recorded during the intervention phase, and during the control phase, a checklist will be used (eg, frequency of symptom assessments T0–T2 (figure 2)).

Drug consumption for all types of symptom relief. These data will be collected from the patients’ medical records.

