## Introduction

Children with cancer struggle with several physical and emotional symptoms. Their ability to communicate these symptoms is dependent on various factors such as age, maturity, diagnosis, cognitive status, psychological status, language ability and cultural background as well as situational aspects. Alleviating distress caused by cancer is beneficial for both children, their families and healthcare professionals^1^. Symptom identification and communicative support can enable symptom relief with the potential to reduce distress and alleviate suffering for the child and will also improve quality of the care.^1^

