### Distress in children

The term ‘distress’ refers to a multifactorial unpleasant emotional experience that can be described as a combination of fear, anxiety and pain.^21^ The relationships between these factors are complex, and the experience of distress is based on interactions between ‘genetically linked behaviour patterns, temperamental predispositions, normal developmental fears, parental psychopathology and discrete learning experiences’.^22^ Distress in this study is defined as an experiential response and sensation of the mind associated with negative emotions that appear when a situation is fearful or impossible to manage from the perspective of the child. Distress can be a consequence of insufficient symptom relief, and self-reported distress is a global assessment that reflects the child’s experience of the success of symptom relief. It is important to evaluate the distress in children undergoing cancer treatment and to find strategies for the measurements of symptoms/emotions that are reliable and valid for this purpose. It is known that acute stress activates the hypothalamic–pituitary–adrenal axis and the sympathetic nervous system as well as the hypothalamic–pituitary–gonadal axis.^23–25^ For example, plasma cortisol concentration is an established stress (energy mobilisation) indicator that is known to react within minutes after the onset of stress exposure. Estradiol is on the other hand an anabolic hormone, which protects against adverse effects of stress.

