### Hypothesis

Children undergoing cancer treatment will experience lower distress levels, when they can report their holistic symptoms in a system created using universal design principles (ie, the PicPecc tool with pictorial support) than will children with standard healthcare communication opportunities (the primary outcome). In addition to a decrease in self-reported stress levels, there will also be a decrease in neuropeptides, neurosteroids and peripheral steroids for stress and pain.Person-centred care is enhanced, through enabling children to proactively assess their symptoms from a holistic perspective and communicate these to their healthcare providers within an enhanced communication framework (ie, using the PicPecc tool).

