### Intervention

In the intervention phase, the child will use the PicPecc tool before and during high-dose methotrexate treatment for communicative support to assess their symptoms and emotions. The PicPecc tool is used in a phone or a tablet computer; delivered via an iOS or Android platform. The development of the PicPecc tool is presented elsewhere.^34^ The PicPecc tool is based on a child-centred assessment approach, and the goal is to adapt the assessment to the child’s age, maturity, diagnosis, language ability and cultural background. All sections of the PicPecc tool will contain pictures, text and sound. The PicPecc tool includes an assessment scale, which is designed as a thermometer. The thermometer is graded from 0 (green) to 10 (red). Each level of the scale is also symbolised with a face that shows the intensity of each symptom and/or emotion. The result of the assessment is visualised as a facial expression and colour that represents the intensity of the symptom and/or emotion (ie, anxiety, appetite, fear, how I am feeling today, nausea, pain and sleep). In addition, the PicPecc tool has a body outline without any markings on which the child can indicate the location of the symptom and/or emotion, pictures for the type of symptom and/or emotion as well as open questions where the child can write narratives about symptoms and/or emotions. The child receives visual feedback from the app and directly from healthcare professionals participating in the intervention, on their reported assessments made with the thermometer. The child can follow the assessments on an hourly, daily or weekly basis. The PicPecc tool also includes a personal avatar to represent the child. Using the avatar the child can make choices of the avatar’s gender, skin and hair colour, and its facial expressions thus contributing to the inclusiveness of the PicPecc tool by providing racial and gender diversity. The avatar will be linked to the child throughout all the assessments. In addition, in order to enhance interaction with the tool the design of the app includes a gamification element, for example, the child will get a reward in the form of a pet when he/she has assessed the symptoms and/or emotions (figures 3–5). The child is encouraged with a reminder in the PicPecc tool to assess the symptoms and/or emotions two times per day (in the morning and in the evening). The child can in addition assess his/her symptoms and/or emotions more frequently with the PicPecc tool, for example, if he or she prefers to do so.

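### The crossover does not by itself let a between-phase difference in plasma steroids be read as a stress effect, because glucocorticoid drugs given after phase allocation are not linked to the biomarker samples

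*Protocol article*

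**What the plan says.** The Distress in children section gives the reason for the biomarkers: "plasma cortisol concentration is an established stress (energy mobilisation) indicator that is known to react within minutes after the onset of stress exposure". The Hypothesis section states the expected direction, namely that besides lower self-reported stress "there will also be a decrease in neuropeptides, neurosteroids and peripheral steroids for stress and pain".

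Under Measures and materials, Secondary outcomes, blood is taken in each phase at T-1 and T0 (before methotrexate) and at T1 and T2 (24 and 48 hours after its start). The same item states one limit, "It is not possible to distinguish between different types of stress". It then concludes that, because the same child is assessed before and after chemotherapy with and without the tool, "it is possible to evaluate the effect of the PicPecc tool on intervention-related stress". Drug effects on the measured steroids are not mentioned.

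A separate item in that list reads "Drug consumption for all types of symptom relief. These data will be collected from the patients’ medical records". Nothing connects it to the blood samples. The Selection criteria do not mention steroid drugs. The Data analyses plan names a paired t-test at p < 0.05.

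**The concern.** A within-child comparison cancels what is constant in the child. It does not cancel what differs between the two phases, least of all what differs because of the intervention. Treatment of symptoms is a factor of that kind. The Introduction says "Symptom identification and communicative support can enable symptom relief", and the tool asks the child to rate "anxiety, appetite, fear, how I am feeling today, nausea, pain and sleep" and feeds the ratings back to staff. The protocol makes drug consumption an outcome, so it accepts that drug use may differ by phase.

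If some of the drugs given are glucocorticoids, cortisol falls in the treated children whatever their stress. A difference in use between phases would then appear as a difference in cortisol, and the plan would read a fall as less stress. The opposite difference in use could hide a real benefit. At stake is whether the biomarker result can support or contradict the self-reported one.

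**Working it through.** **Number of pairs.** The plan's own figure reproduces. Take a paired t-test with difference 1.5, SD 2.9 read as the SD of within-child differences, and two-sided alpha 0.05 (sidedness is not stated). Power is 0.796 at n = 31 and 0.809 at n = 32, so 32 is the smallest adequate n, and 32 / 0.8 = 40. This sizing is for the distress score. It is used here only to fix the number of pairs.

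**Inputs that the document does not give.** It has no figure for glucocorticoid use, cortisol suppression or cortisol variability. Suppression of cortisol by glucocorticoids is general pharmacology, not taken from the text. Everything below is illustration on assumed inputs.

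**Size of a spurious shift.** Let true stress be equal in both phases, mean cortisol be 100 in an unexposed child, *s* the suppression in an exposed child and *p* the share exposed in a phase.

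Phase mean = 100 × (1 − *s* × *p*)

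| *s* | *p* control | *p* PicPecc | Control mean | PicPecc mean | Apparent change |
|---|---|---|---|---|---|
| 80% | 20% | 30% | 84 | 76 | 76/84 − 1 = −9.5% |
| 80% | 30% | 20% | 76 | 84 | 84/76 − 1 = +10.5% |
| 80% | 20% | 40% | 84 | 68 | 68/84 − 1 = −19.0% |
| 80% | 40% | 20% | 68 | 84 | 84/68 − 1 = +23.5% |
| 50% | 20% | 30% | 90 | 85 | 85/90 − 1 = −5.6% |
| 50% | 30% | 20% | 85 | 90 | 90/85 − 1 = +5.9% |
| any | equal | equal | equal | equal | 0 |

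The step from 20% to 30% is 4 more children of 40.

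**Chance of a significant result with no stress effect.** This was simulated with 32 pairs and 20,000 trials per setting. Within-child differences in log cortisol were normal with an assumed SD of 0.5 or 0.8. A given share of children was exposed in the PicPecc phase only, and a two-sided paired t-test was applied. The entries are the chance of significantly lower cortisol under PicPecc.

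| Extra children exposed | SD 0.5, *s* 50% | SD 0.5, *s* 80% | SD 0.8, *s* 50% | SD 0.8, *s* 80% |
|---|---|---|---|---|
| 0% | 2.5% | 2.4% | 2.3% | 2.7% |
| 10% | 10% | 21% | 7% | 14% |
| 20% | 26% | 58% | 14% | 39% |
| 30% | 48% | 87% | 26% | 68% |

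By symmetry, the same chances apply to significantly higher cortisol if the extra exposure falls in the control phase.

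**What the design does and does not remove.** Random order balances steroids scheduled by the leukaemia protocol on average. If they fall in only one of a child's two phases, they still add noise to that pair. Random order does not balance drugs given in response to symptoms, because these follow allocation. The T-1 and T0 samples can reveal exposure already present at baseline, but not exposure that begins between T0 and T2.

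**The case against.** The strongest reply has four parts.

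- **Drug use is recorded.** A reader might infer that the plan takes no account of drugs. The text does not support that, because consumption of symptom-relief drugs is collected from the records in this study. Linking or adjusting for it could sit in an analysis plan that is not shown, so a missing adjustment is not the point. What remains is that the article asserts the attribution on the own-control argument alone. The record is also described as covering symptom relief, which need not include glucocorticoids given against the leukaemia.
- **Exposure and direction are assumed.** A reader might infer that the bias favours the tool. The document does not say that these children receive glucocorticoids, and it predicts no direction for drug use. Better communication could raise use, lower it or change the drugs chosen, and the first table is close to symmetric. This part stands in full.
- **The setting is standardised.** The article chose a strictly scheduled treatment, randomises the order and samples before methotrexate in each phase. These features limit the problem for scheduled steroids and for exposure visible at baseline, but not for symptom-driven use during the phase. The first table compares raw phase means and takes no credit for baseline samples. For a change-from-baseline analysis it applies to exposure starting after T0.
- **Restricting the analysis has its own bias.** It is tempting to make glucocorticoid-free pairs the main analysis. Exposure arises after allocation and may be affected by the tool, so this would break the randomised comparison and might drop the most symptomatic children. This objection also stands, and the fix respects it.

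**Conclusion.** The point holds as a limit on interpreting a secondary outcome. The own-control argument does not justify the unqualified claim about stress, because drug exposure that arises after allocation can move cortisol in either direction. On assumed suppression of 80%, a difference of ten percentage points in use (20% versus 30%) shifts mean cortisol by about 10%, downwards or upwards according to which phase has more use. At 50% suppression the shift is about 6%, and with equal use it is zero. Whether any such difference will occur cannot be told from the document.

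A reader might go further and infer that a fall in steroids would be an artefact, or that the trial's main conclusion is at risk. Neither follows. The illustration covers cortisol only, whereas the hypothesis also names neuropeptides and neurosteroids. The article presents the biomarkers beside self-report as one of two stress indicators. The primary distress score and the sample size of 32, or 40 with dropout, are unaffected.

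**What to change.** - From the medical records already being reviewed, extract the drug and time of every systemic glucocorticoid, for any indication, in a fixed window before T-1 and up to T2 in both phases.
- Keep all pairs as the main biomarker comparison and report glucocorticoid use by phase beside it.
- Add a sensitivity analysis that excludes or flags exposed samples, and say that this subset is selected after allocation and is not a randomised comparison.
- Reword the closing claim of the blood-sample item so that a fall in cortisol or other steroids is not attributed to lower stress unless it is consistent across these analyses.

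The cost is one more extraction field, one more analysis and fewer pairs in the sensitivity analysis. Patient treatment does not change.

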### Process evaluation

After each intervention, experiences of care during the treatment are explored in individual semistructured interviews (T3) with all participating children, their legal guardians and the healthcare professionals involved in the children’s care. The objective is to illuminate the experiences of using the PicPecc tool from the perspective of the participating children, their legal guardians and the healthcare professionals. The interviews will be thematically analysed following the procedures of Braun and Clarke^46^ to give an understanding of how the PicPecc tool was used during the intervention.

Numerical data regarding when and how often the children used the PicPecc tool will also be collected.

The semistructured interviews will follow an interview guide adapted for the child according to age and maturity. The questions will also be provided with pictorial support according to the concept of universal design (online supplemental file 1). The child and the legal guardian are interviewed separately. The aim is to interview both the child and their legal guardian; however, if either of them is unwilling or does not fit the criteria the other (child or legal guardian) will be invited to participate on their own.

10.1136/bmjopen-2020-042726.supp1Supplementary data

### Intervention

In the intervention phase, the child will use the PicPecc tool before and during high-dose methotrexate treatment for communicative support to assess their symptoms and emotions. The PicPecc tool is used in a phone or a tablet computer; delivered via an iOS or Android platform. The development of the PicPecc tool is presented elsewhere.^34^ The PicPecc tool is based on a child-centred assessment approach, and the goal is to adapt the assessment to the child’s age, maturity, diagnosis, language ability and cultural background. All sections of the PicPecc tool will contain pictures, text and sound. The PicPecc tool includes an assessment scale, which is designed as a thermometer. The thermometer is graded from 0 (green) to 10 (red). Each level of the scale is also symbolised with a face that shows the intensity of each symptom and/or emotion. The result of the assessment is visualised as a facial expression and colour that represents the intensity of the symptom and/or emotion (ie, anxiety, appetite, fear, how I am feeling today, nausea, pain and sleep). In addition, the PicPecc tool has a body outline without any markings on which the child can indicate the location of the symptom and/or emotion, pictures for the type of symptom and/or emotion as well as open questions where the child can write narratives about symptoms and/or emotions. The child receives visual feedback from the app and directly from healthcare professionals participating in the intervention, on their reported assessments made with the thermometer. The child can follow the assessments on an hourly, daily or weekly basis. The PicPecc tool also includes a personal avatar to represent the child. Using the avatar the child can make choices of the avatar’s gender, skin and hair colour, and its facial expressions thus contributing to the inclusiveness of the PicPecc tool by providing racial and gender diversity. The avatar will be linked to the child throughout all the assessments. In addition, in order to enhance interaction with the tool the design of the app includes a gamification element, for example, the child will get a reward in the form of a pet when he/she has assessed the symptoms and/or emotions (figures 3–5). The child is encouraged with a reminder in the PicPecc tool to assess the symptoms and/or emotions two times per day (in the morning and in the evening). The child can in addition assess his/her symptoms and/or emotions more frequently with the PicPecc tool, for example, if he or she prefers to do so.

**Figure 3 F3:**
[figure not shown]
The PicPecc tool consists of an avatar and pets that the child can win through interaction with the reporting process. PicPecc, pictorial support in person-centred care for children.

**Figure 4 F4:**
[figure not shown]
Reports are made by using a thermometer for assessing symptoms and emotions.

**Figure 5 F5:**
[figure not shown]
The child receives feedback on the assessments in the form of diagrams showing the results of the latest days or weeks.

### The implementation of a person-centred approach in both phase A and phase B

The implementation strategies of person-centred communication consist of two components:

A person-centred workshop for the paediatric oncology teams about enhanced symptom communication.One member of the research team will be assigned to coach their colleagues in each of the clinical departments on the person-centred approach. They will support the implementation of the intervention and be responsible for data collection.Workshops with paediatric oncology teams.

Paediatric oncology teams will be invited to a workshop that will scrutinise and discuss communication issues based on five questions (figure 6). These questions will be: how communication, based on a person-centred approach, can be implemented in clinical practice in child healthcare?

**Figure 6 F6:**
[figure not shown]
The questions will be discussed step by step in the workshops with communication and symptom management. PicPecc, pictorial support in person-centred care for children.

### Clinical coaches to support the implementation of the intervention

One coach in each of the clinical departments will support the implementation of the intervention. The coach will be responsible for facilitating education and support for their colleagues in the clinical department. In addition, the coaches will also be responsible for data collection. The coach in each clinical ward will get support with the research process from the research group.

### Procedural fidelity

The procedural fidelity will be evaluated in each phase. The coach will (a) monitor the occurrence of relevant variables, (b) provide documentation that the experimental conditions occurred as planned, (c) provide support to practitioners about the use of the interventions.

### Data analyses plan

#### Effect evaluation

We expect the intervention to be superior to the control in terms of the health outcome assessment (NRS-11). We also expect that there will be a difference between premethotrexate treatment (T1, T0) and methotrexate treatment (T1, T2) in both intervention and control phases. Therefore, we will test the null hypothesis that there will be neither change in any of the measurements between the premethotrexate treatment (T-1, T0) and methotrexate treatment (T1, T2) nor between intervention and control phases. A p value of <0.05 will be considered as statistically significant. Categorical data will be descriptively analysed by frequency distributions and percentages. The paired sample t-test will evaluate the difference between two sets of assessments and effect size.^47^ Data will be analysed with IBM SPSS Statistics V.25 (New York City, USA).

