## Methods and analysis

### Study design

The Medical Research Council’s key principles and actions for development and evaluation of complex interventions^29 30^ guided the intervention development and the research design. In a hybrid design, both the effects of the intervention and the implementation process will be evaluated.^31^ Relevant care situations are selected^32^ where highly standardised care procedures are used and where there is a range of different situations where children struggle with symptoms. To facilitate the effect evaluation, the children will participate in a crossover design study where they are their own controls (figure 1). The study design follows the SPENT 2019 checklist for clinical trials.^33^

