**Figure 1 F1:**
[figure not shown]
The cross-over design with two study groups will participate in two phases as related to the Nordic and European study protocols in Sweden for treatment of children with high-dose methotrexate. All methotrexate treatment sessions take a similar amount of time for the child. The intervals between each of the methotrexate treatments will be controlled by each child’s treatment plan and may vary between 3 and 6 weeks. NRS, numeric rating scale; PicPecc, pictorial support in person-centred care for children.

The development of the PicPecc tool follows established guidelines^34^ and was based on the theoretical framework of person-centred care,^4^ on published systematic reviews^9^ and on systematic reviews conducted within the project on assessment tools for nausea,^35^ and anxiety.^36^ Children with cancer, their legal guardians and healthcare professionals have been involved throughout the development process. The study protocol outlined here pertains to the evaluation and implementation phases.

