### Randomisation

The participants will be allocated codes in a consecutive order; the code is randomly assigned to either the intervention phase (B) or control phase (A). Participating cancer units will be given the solution to the randomisation code once the codes have been allocated to the participants. The participants will only have access to the PicPecc tool during the intervention phase. There will be a period of at least 2 weeks between the end of the first intervention period and the start of the next methotrexate treatment. This provides an adequate washout period between the intervention (B) and the control phase (A) for any behaviour change to revert to previous patterns. Following the transtheoretical model,^40^ habitual behaviour change related to health is a process involving a number of stages that takes time to complete successfully, where support for change is removed early in the process the individual will quickly revert to previous habituated behavioural patterns. We are confident, therefore, that the intervention will have no residual effects on the control phase.

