### Measures and materials

#### Impact evaluation

We consider a difference of 15% to be a meaningful difference in score average between T0 and T2 (48 hours); this is represented by a difference of approximately 1.5 units on the NRS (0–10) of distress, when comparing users of the PicPecc tool to control subjects. The estimate of SD is based on unpublished data of 11 to 12-year-old girls’ self-reports.^41^ Based on an expected SD of 2.9 (and a power of 0.8), it is necessary to include at least 32 participants. With a dropout rate of approximately 20%, 20 participants in each group, that is, 40 participants will be included in the study.

In both the control (A) and intervention phases (B), the data collection follows the test period outline in figure 2. Assessment of distress will be made at time points T-1, T0, T1 and T2. T3 is an interview to evaluate the implementation process. Primary outcome is the difference in delta T0 and T2 between control and intervention phases. The time points are linked to the schedule for the methotrexate treatment to avoid extra blood sampling. The time points will also facilitate the evaluation between before and after treatment, with the objective to evaluate differences in symptoms, with and without the PicPecc tool (figure 2).

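### The randomised crossover is analysed with a plain paired t-test that has no period term, so any period effect on the T0–T2 change costs power and, with unequal sequences, shifts the estimate

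*Protocol article*

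**What the plan says.** The Figure 1 caption describes the design: "The cross-over design with two study groups will participate in two phases". The Study design section adds that "the children will participate in a crossover design study where they are their own controls". Under Randomisation, consecutive codes are issued and "the code is randomly assigned to either the intervention phase (B) or control phase (A"). No blocking or stratification is described, although the sample size paragraph under Impact evaluation plans 20 children per group.

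The two phases fall on different methotrexate courses, and the interval between courses "may vary between 3 and 6 weeks" (Figure 1 caption). The endpoint is set under Impact evaluation: "Primary outcome is the difference in delta T0 and T2 between control and intervention phases".

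For inference, the Effect evaluation part of the Data analyses plan gives one method: "The paired sample t-test will evaluate the difference between two sets of assessments and effect size". The article nowhere mentions a period or sequence term. The washout argument under Randomisation concerns carry-over only.

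**The concern.** Randomising the order allows a difference between first and second courses to be separated from the effect of PicPecc. A paired t-test on the PicPecc-minus-control differences does not use that information. If distress changes differently over 48 hours in the second course than in the first, children who have PicPecc second carry that period effect with one sign, and children who have it first carry it with the other.

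Two things follow. The spread between the two sequences enters the error variance, so power falls. And if the sequences do not finish with equal numbers, the plus and minus terms no longer cancel, and part of the period effect stays in the treatment estimate. The design has almost no spare power (0.81 against a target of 0.80), so a moderate period effect is enough to take the primary test below target.

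This is not a detail left to an unseen analysis plan. The article commits to a method, and that method does not use the randomised order.

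**Working it through.** **Inputs from the article (Impact evaluation; Effect evaluation).** Target difference 1.5 units ("this is represented by a difference of approximately 1.5 units on the NRS (0–10) of distress"), SD 2.9, power 0.8, 32 evaluable, 20% dropout, 40 enrolled as 20 per group, significance level 0.05. Sidedness is not stated.

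**Reproducing the plan's figure.** For a paired t-test, two-sided 0.05, with 2.9 taken as the SD of the within-child differences:
- Normal approximation: [(1.960 + 0.842) × 2.9 / 1.5]² = 29.3, so 30.
- Noncentral t: N = 32, power 0.809. This matches the plan. A one-sided test would give 25.
- Dropout: 32 / 0.8 = 40. This matches.

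**Model for the check.** Let τ be the treatment effect and π the period effect on the T0–T2 change (second course minus first). The PicPecc-minus-control difference has mean τ + π in children who have control first (n1) and τ − π in children who have PicPecc first (n2), with SD 2.9 within each sequence. The article gives no π, so 0.5 to 2 NRS units is an assumed range.

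**Balanced completers, 16:16.** The mean difference is τ, so there is no bias. The SD that the paired test sees is √(2.9² + π² × 32/31). For example, at π = 1.5 it is √(8.41 + 2.32) = 3.28. Power and type I error are from 50,000 simulated trials per scenario.

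| π | SD seen by paired test | Paired power | Power with period term | Paired type I error |
|---|---|---|---|---|
| 0.5 | 2.94 | 0.80 | 0.81 | 0.047 |
| 1 | 3.07 | 0.77 | 0.81 | 0.037 |
| 1.5 | 3.28 | 0.73 | 0.81 | 0.028 |
| 2 | 3.54 | 0.67 | 0.81 | 0.019 |

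To regain 80% power, the paired test would need about 33, 35, 40 and 46 evaluable children.

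**Unequal completers.** Conditional on the split, bias = π × (n1 − n2)/N.
- 18:14: π × 4/32 = 0.125π, which is 0.06, 0.125, 0.19 and 0.25 units for π = 0.5, 1, 1.5 and 2. Paired type I error is 0.049, 0.045, 0.039 and 0.032, all at or below nominal. At π = 1, paired power is 0.84 or 0.70, depending on the direction of the period effect, against 0.80 adjusted.
- 20:12: π × 8/32 = 0.25π. Paired type I error is 0.053, 0.063, 0.071 and 0.079 over the same range.

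**How likely are such splits among 32 completers?**

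| Split | From exactly 20/20 with 8 random dropouts (hypergeometric) | Simple randomisation (binomial) |
|---|---|---|
| 18:14 or worse | 24% | 60% |
| 20:12 or worse | 0.3% | 22% |

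**Cost of adjusting when π = 0.** At 16:16 the period-adjusted test has 30 degrees of freedom instead of 31. Power is 0.808 instead of 0.809, and the required N remains 32.

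**The case against.** The best defence is that the paired test may do little harm here.

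- The endpoint is a change within each phase, so anything that moves T0 and T2 together cancels. Practice with the rating scale or ward coaching may act that way. Only a period effect on the 48-hour change matters, and the article supplies no evidence of one. **This stands.** It is why the size is given as a range; at π = 0.5 the loss is about one percentage point of power.
- With equal sequences the paired estimate is unbiased, and over repeated randomisations the bias averages to zero. **This stands.** The bias applies to the split actually obtained.
- A reader might infer that the paired test inflates false positives. The documents do not support that as a general statement. Averaged over 20/20 allocation with random dropout, its type I error is 0.047, 0.041, 0.032 and 0.023 for π = 0.5, 1, 1.5 and 2. Under simple randomisation it averages about 0.05. Inflation appears only given a split such as 20:12, which is very unlikely if the planned 20 per group is achieved and dropout is unrelated to sequence.
- A reader might also count carry-over against the paired test, given the statement "We are confident, therefore, that the intervention will have no residual effects on the control phase". That is a separate assumption. A model with treatment and period terms has the same carry-over bias as the paired test, so doubts about the washout are no argument for this change.

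What the defence does not answer is why the primary analysis should leave out the randomised order when including it costs almost nothing.

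**Conclusion.** The point holds as a should-fix. The named analysis does not match the randomised two-period design. Its main cost is lost power through a conservative test: from negligible at a period effect of 0.5 units to 14 percentage points (0.67 against 0.81) at 2 units, with 16:16 completers. A secondary cost is a bias of one eighth of the period effect at 18:14, a split at least that uneven having probability 24% or 60%, depending on how allocation is done.

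These figures assume normally distributed differences, 32 complete pairs, 2.9 as the SD of between-phase differences within a sequence, dropout unrelated to sequence and no carry-over. The period effect itself is unknown. If it is zero, the paired test is valid. The documents do not show that a period effect is likely on this endpoint, nor that the trial's false-positive rate is raised.

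**What to change.** In the Effect evaluation part of the Data analyses plan, replace the paired t-test for the primary outcome with a period-adjusted crossover analysis. Either of these will do:

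- a two-sample t-test comparing the within-child period differences (second phase minus first, in the T0–T2 change) between the two randomised sequences, with half the difference in means as the treatment estimate; or
- a linear mixed model for the T0–T2 change with fixed treatment and period effects and a random child effect.

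Name one as primary before outcome data are examined by phase.

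The cost is a change of wording and one degree of freedom. The targets of 32 evaluable and 40 enrolled children stand. With 16:16 completers, power stays at about 0.81 whatever the period effect; at 18:14 it is about 0.80 and at 20:12 about 0.78. The change leaves the no-carry-over assumption under Randomisation as it is.
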